### Statistical analysis

#### Sample size

For calculations relating to the primary objectives of a measured difference between standard care and LCP for:

Number and percentage of cancer patients discharged: results from thresholds defined for discharge in a previous study are used.^7^ Based on previous data within the cancer group, assuming for the discordant pairs that the Brock model threshold (representing the standard of care) identified 0.4% of cancers for which the LCP threshold would have recommended discharge, and the LCP threshold correctly identified 2.6% of cancers for which the Brock model threshold would have recommended discharge, then using McNemar’s test with 90% power and a significance level of 0.05, 659 participants would be needed. However, with a sample size of 2000, there is 90% power to detect a difference between the methods if the percentages were as small as 1.0% and 2.3%, respectively.Number and percentage of benign-nodule patients discharged: again, results from thresholds defined for discharge in a previous study are used.^7^ Based on previous data within the benign group, assuming for the discordant pairs that 17.0% of benign nodules are recommended for discharge by the LCP threshold but not by the Brock model threshold. In comparison, 13.5% are recommended for discharge by the Brock model threshold but not by the LCP threshold; there is 80% power to detect a significant difference between the two tests with 2026 individuals using McNemar’s test. This equates to an OR of 1.26

Sample size calculations were performed using R statistical software (V.4.1.2; R Foundation for Statistical Computing, Vienna, Austria).

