## Abstract

**Introduction:**

In a small percentage of patients, pulmonary nodules found on CT scans are early lung cancers. Lung cancer detected at an early stage has a much better prognosis. The British Thoracic Society guideline on managing pulmonary nodules recommends using multivariable malignancy risk prediction models to assist in management. While these guidelines seem to be effective in clinical practice, recent data suggest that artificial intelligence (AI)-based malignant-nodule prediction solutions might outperform existing models.

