### Design and setting

DOLCE is a multicentre prospective observational cohort study recruiting patients with 5–30 mm solid and part-solid pulmonary nodules incidentally detected on thoracic CT scans performed as part of routine practice. The study aims to recruit 2000 patients from 12 centres.

Patients will be asked to consent to and be enrolled at twelve acute NHS hospital trusts in England. A recruitment period of 1 year is planned, with 1 year of follow-up to collect data and ascertain the ground-truth diagnosis of recruited patients.

The start date was March 2023 with the planned recruitment end date being February 2024. With 1 year of follow-up, this will mean a planned end date of February 2025.

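### The 90% power claimed for cancer patients discharged counts all 2000 enrolled patients as cancers, although the rates behind it are percentages of cancers

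*Protocol article*

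**What the plan says.** The Sample size section treats the two halves of the primary objective separately. For cancer patients discharged, the inputs are introduced as "Based on previous data within the cancer group". The Brock threshold, standing in for standard care, is assumed to have "identified 0.4% of cancers for which the LCP threshold would have recommended discharge", and in the other direction "the LCP threshold correctly identified 2.6% of cancers for which the Brock model threshold would have recommended discharge". The calculation uses McNemar's "test with 90% power and a significance level of 0.05, 659 participants would be needed". The next sentence adds that "with a sample size of 2000, there is 90% power to detect a difference between the methods" even with the smaller contrast of 1.0% and 2.3%.

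The Design and setting section says what the 2000 is: "The study aims to recruit 2000 patients from 12 centres". These are patients with incidental solid or part-solid nodules of 5–30 mm, whatever the eventual diagnosis. Table 1 defines the outcome as the number and percentage discharged among cancer patients. The Abstract says "In a small percentage of patients, pulmonary nodules found on CT scans are early lung cancers", and the Introduction describes nodules as benign much more commonly than malignant. No figure for the cancer share appears.

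**The concern.** The unit changes between the inputs and the power statement. The rates have cancers as denominator and the outcome is analysed in cancer patients, so the n in McNemar's formula must be a number of cancers. The power statement puts total enrolment in that place.

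Cancers discharged after the baseline scan are the safety half of the primary objective, in a study meant to inform whether the tool should become standard of care. The printed power tells readers that this half can detect a difference of 1.3 percentage points with 90% power. The article's only caveat about sample size, in its strengths and limitations box, is confined to some secondary objectives.

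**Working it through.** **Inputs.** Discordant rates 0.4%/2.6% and 1.0%/2.3%, 90% power, alpha 0.05, n = 659 and n = 2000 (Sample size); two-sided testing (Statistical analysis); enrolment of 2000 (Design and setting). The cancer share is not given and is assumed below.

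**Formula.** With s the sum of the two discordant rates and d their difference:

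- n = [1.960·√s + 1.282·√(s − d²)]² / d²
- power = Φ{[d·√n − 1.960·√s] / √(s − d²)}

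**Step 1: reproduce the stated figures.**

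- 0.4%/2.6%: s = 0.030, d = 0.022. n = (0.3395 + 0.2202)² / 0.000484 = 647. The article states 659, within 2%.
- 1.0%/2.3% at n = 2000: s = 0.033, d = 0.013. (0.5814 − 0.3560) / 0.1812 = 1.244, so power is 89%. Enumerating over discordant pairs gives 90% for the uncorrected McNemar test and 88% for the exact test. The article states 90%.

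The arithmetic is sound, but 2000 was entered where the number of cancers belongs.

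**Step 2: replace 2000 by the number of cancers.** The share is an assumption. Expected discordant pairs are 3.3% of the cancers for 1.0%/2.3% and 3.0% for 0.4%/2.6%.

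| Assumed share | Cancers | Expected discordant pairs at 1.0/2.3 | Power 1.0/2.3, normal | Power 1.0/2.3, exact | Power 0.4/2.6, normal | Power 0.4/2.6, exact |
|---|---|---|---|---|---|---|
| 5% | 100 | 3.3 | 11% | 1% | 24% | 3% |
| 10% | 200 | 6.6 | 17% | 7% | 43% | 25% |
| 15% | 300 | 9.9 | 24% | 14% | 60% | 49% |
| 20% | 400 | 13.2 | 30% | 21% | 72% | 67% |
| 33% | 660 | 21.8 | 45% | 37% | 91% | 91% |
| 50% | 1000 | 33.0 | 62% | 56% | 98% | 99% |

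The stated calculation implies 2000 × 0.033 = 66 discordant cancers.

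**Step 3: why the two methods part at the top of the table.** If all m discordant pairs favour one method, the exact two-sided p is 2 × 0.5^m: 0.0625 for m = 5 and 0.031 for m = 6. With about 3 pairs expected, the exact test can seldom reject. At 100 cancers the normal formula also flatters the uncorrected test, for which enumeration gives 8% and 18% against 11% and 24%.

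**Step 4: what the stated figures would require.** 659/2000 = 33% of enrolment would have to be cancers. At a 10% share, 659 cancers correspond to 659/0.10 = 6,590 enrolled and 2000 cancers to 20,000.

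**Step 5: cross-check within the section.** The benign half asks for 2026 individuals with rates expressed among benign nodules. Benign and malignant are separate classes under Ground truth diagnosis, so 2000 enrolled patients cannot supply 2000 cancers and 2026 benign patients.

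**The case against.** **The percentages might be shares of all participants.** The 2000 would then be the right n. The section's own wording, that the rates are within the cancer group and of cancers, excludes this reading.

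**The cancer share is unknown.** This stands as a limit on size. The Abstract's remark concerns nodule patients in general, whereas the eligibility criteria select patients aged 35 or over with nodules of 5–30 mm, solid or with a solid component of at least 80%. Their share could be higher than the remark suggests. It cannot approach 100%, which the 1.0%/2.3% claim needs.

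**Stronger readings that the article does not support.** A reader might infer that 659 cancers cannot be reached. The wording makes a 33% share unlikely but does not disprove it. A reader might also take the article to claim 90% power for 0.4%/2.6% with 2000 enrolled. It says only that 659 are needed, so the lower power at that contrast is a consequence to be stated and does not refute a printed figure. Nor does the article claim equal safety or non-inferiority. It promises an OR with a 95% CI and the numbers analysed by group, so readers of the results will see how few cancers there are.

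**McNemar is a proxy.** The planned analysis is conditional logistic regression with a Wald test, so the table only approximates its power. The article itself uses McNemar for sizing, and the unit error is the same under either method.

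**Conclusion.** The statement of 90% power at 1.0%/2.3% with 2000 is wrong as written. It holds only if essentially every enrolled patient has cancer, and at any share up to one half the power is at most about 62% (56% exact). This conclusion needs no assumed share, only the article's own statement that most nodules are benign.

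How far power falls short does depend on an assumption. Over shares of 5 to 20%, power at 1.0%/2.3% runs from about 11 to 30% by normal approximation and 1 to 21% by the exact test. At the larger contrast of 0.4%/2.6% it runs from about 24 to 72% and 3 to 67%. Indeterminate diagnoses would reduce the number of confirmed cancers further. The 659 is a correct order of magnitude with the wrong label: it counts cancers, not enrolled participants.

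**What to change.** In the Sample size section:

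- Withdraw the claim of 90% power at 1.0%/2.3% with 2000.
- Label 659 as cancer patients.
- State the assumed cancer share, its source, and the expected number of cancers among 2000.
- Give the power at 0.4%/2.6% and the detectable difference for that number, by an exact or simulation method because few discordant pairs are expected.

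The planned OR with 95% CI should stay; nothing here calls for another effect measure. A sentence that a non-significant result is not evidence of equal safety would be useful but is optional.

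The cost is wording and a short recalculation. Recruitment, data collection and the analysis do not change, but the stated power for this half of the primary objective becomes less favourable.

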### Ground truth diagnosis

Patients will be classified into whether they have benign or malignant nodules as follows:

Benign-nodule patients:By resolution or stability of all qualifying incidental pulmonary nodules as determined from volumetry-based measurement on imaging follow-up over 12 months.By histopathology from biopsy or surgery of all qualifying incidental pulmonary nodules (within 12 months of baseline CT scan).Malignant-nodule patients:By histopathology from biopsy or surgery (within 12 months of baseline CT scan) of at least one qualifying incidental pulmonary nodule.Probable benign-nodule patients:By resolution, stability or shrinkage of qualifying incidental pulmonary nodules that are not in ground-truth outcomes #1 or #2 above as determined from volumetry-based measurement on imaging follow-up conducted between 3 and 12 months after the baseline CT scan.By resolution, stability or shrinkage of qualifying incidental pulmonary nodules that are not in ground-truth outcomes 1 or 2 above as determined from diameter-based measurement on imaging follow-up conducted 12 months after the baseline CT scan (supplemented with a volume-based measurement of the nodule that will be performed for research purposes).Probable malignant-nodule patients:By clinical diagnosis of lung cancer, in whom a biopsy or resection is not possible, based on high clinical probability and who are registered at a lung cancer MDT/and/or receive non-surgical treatment (stereotactic ablative radiotherapy (SABR)/radiotherapy/microwave ablation).

Volumetry-based measurement of nodule stability—and hence a benign diagnosis—will be satisfied if the lung nodule volume on the follow-up CT scan was <125% of the lung nodule volume on the baseline CT scan.

If the standard care at a particular site does not incorporate volumetry-based measurements, the volumetric measurement will be applied as part of the research study to the relevant follow-up CT scans.

Any lung nodule patients who do not fall into either of the two ground-truth outcomes 1 or 2 above will be considered to have an indeterminate diagnosis at the time of analysis and will be analysed with and without the inclusion of the ground-truth outcomes in 3 and 4.

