#### Statistical analysis

Statisticians will carry out all analyses. For each outcome measure, the following will be reported:

The number of participants included in the analysis, stratified by the relevant group.Mean or median (SD or IQR) for continuous outcomes, and numbers and proportions (percentage) for binary outcomes.An effect size (OR) with a 95% CI.A two-sided p value.

For both primary objectives, measured differences between standard care and the LCP options for patients with cancer diagnosed and benign-nodule patients discharged will be analysed using conditional logistic regression. Statistical significance will be assessed with a Wald test. Secondary outcomes will be described and analysed according to their distribution. All outcomes will have an exact p value provided for them so the reader can access the data for significance level, so correction for multiple testing should not be needed.

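### The 2026 in the benign-discharge power statement counts benign patients, but the study enrols 2000 patients of all diagnoses, so the planned enrolment does not support the stated 80% power

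*Protocol article*

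**What the plan says.** The Design and setting section of the protocol article fixes the total: "The study aims to recruit 2000 patients from 12 centres". Table 1 has two primary outcomes, discharge among cancer patients and discharge among benign-nodule patients.

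The Sample size section treats each outcome separately. The benign calculation opens with "Based on previous data within the benign group". It assumes that "17.0% of benign nodules are recommended for discharge by the LCP threshold but not by the Brock model threshold" and that "13.5% are recommended for discharge by the Brock model threshold but not by the LCP threshold", and concludes that "there is 80% power to detect a significant difference between the two tests with 2026 individuals" by McNemar's test.

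The Ground truth diagnosis section sorts patients into benign, malignant, probable benign and probable malignant. Anyone outside the first two groups "will be considered to have an indeterminate diagnosis at the time of analysis", and the same sentence plans analyses both including and excluding the two probable groups. The article gives no expected share for any of these groups. The abstract says only that cancers make up a small percentage.

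**The concern.** The number of pairs in a McNemar calculation must be the number of patients to whom the discordant percentages apply. Here those are benign patients with an established diagnosis, so 2026 of them are required. The study will have 2000 patients before any cancer or unclassified patient is set aside, so the condition attached to the 80% cannot be met.

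Benign discharge carries the efficiency case for the tool, because fewer follow-up scans come from discharging benign patients sooner. A reader who takes 80% as the study's power for this outcome would give a null result more weight than it deserves, and the article does not say by how much.

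**Working it through.** **Inputs.**
- p10 = 0.170 and p01 = 0.135, from the benign calculation in the Sample size section. The discordant total is pd = 0.305, the difference is d = 0.035, and the ratio is 0.170/0.135 = 1.26, matching the printed OR.
- Alpha = 0.05. It is printed only for the cancer calculation ("using McNemar’s test with 90% power and a significance level of 0.05") and is assumed to be the same here.
- Two-sided, from the Statistical analysis section ("A two-sided p value").
- Total enrolment is 2000. The share not classed benign is not given, so 5%, 10% and 20% are assumptions.

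**Step 1: reproduce the plan's figure.**

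Uncorrected normal approximation: n = [1.960·√pd + 0.8416·√(pd − d²)]² / d² = [1.960·√0.305 + 0.8416·√0.303775]² / 0.001225 = (1.0824 + 0.4639)² / 0.001225 ≈ 1952.

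With continuity correction: n' = (n/4)·[1 + √(1 + 4/(n·d))]² ≈ 2009.

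Exact test: the number of discordant pairs M is binomial(n, 0.305). Given M = m, the count favouring LCP is binomial(m, 0.170/0.305 = 0.557). The rejection probability of the two-sided exact binomial test is averaged over M. Power passes 80% at about n = 2005 and is 80.4% at n = 2026.

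The stated 2026 is therefore sound for 80% power, provided that it counts benign patients. The one-sided formulas give about 1533 to 1594 and do not reproduce it.

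**Step 2: power at the benign numbers that 2000 enrolled can supply.**

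Normal approximation: power = Φ{[d·√n − 1.960·√pd] / √(pd − d²)}. At n = 1800, for example: (0.035 × 42.43 − 1.0824)/0.5512 = 0.730, and Φ(0.730) = 76.7%.

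| Share not benign (assumed) | Benign patients | Exact | Normal |
|---|---|---|---|
| 0% | 2000 | 79.9% | 81.0% |
| 5% | 1900 | 77.8% | 78.9% |
| 10% | 1800 | 75.5% | 76.7% |
| 20% | 1600 | 70.3% | 71.8% |

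**Step 3: where 80% is lost.** By the exact test, power is already just under 80% at 2000 benign patients. By the uncorrected approximation it holds down to 1952, so at most 2000 − 1952 = 48 patients (2.4%) could be cancers or unclassified.

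**Step 4: definite and probable outcomes.** The table depends only on the number analysed as benign. If probable-benign patients are included, that number is total enrolment less cancers and patients who remain unclassified. If they are excluded, it falls further, by an amount the article does not let one calculate.

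**The case against.** The strongest reply is that the printed sentence is conditional. It attaches 80% to 2026 individuals, which is reproducible, and never says that 2000 enrolled patients deliver it. The planned analysis is also not the exact test. The Statistical analysis section specifies a Wald test from conditional logistic regression, whose power is 81.0% at 2000 benign patients and 80.0% at about 1950. On that test fewer benign patients are needed than will be enrolled in total. If cancers are few and probable-benign patients are included, the shortfall could be a point or two.

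This limits the size of the point but does not remove it. The Wald figures at 1900, 1800 and 1600 are 79.0%, 76.7% and 71.8%, essentially the normal column above. Cancers and unclassified patients remain outside the benign analysis whichever test is used. The article gives no share that would let a reader see how far below 2000 the benign number lies.

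A reader might be tempted by three stronger readings:

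- **Power falls to a fixed level well below 80%.** The documents give no non-benign share, so any single figure is an assumption.
- **Power is only about 62–64%.** This subtracts the 659 of the cancer calculation from 2000, leaving 1341 benign. It requires 659/2000 = 33% cancers, which does not fit the abstract's small percentage. That 659 + 2026 = 2685 exceeds 2000 is true, but if cancers are few it tells mainly against the cancer calculation, which is a separate matter.
- **The calculation is invalid because it uses a Brock threshold instead of actual care.** The Sample size section openly declares Brock as its stand-in for standard care. Whether that proxy is apt does not bear on 2026 against 2000.

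**Conclusion.** The point holds as an unreconciled denominator, not as an arithmetic error: 2026 is a correct benign-patient requirement set beside an enrolment of 2000 patients of all diagnoses. The 80% is therefore not supported by the planned enrolment. The loss is modest if few patients fall outside the benign group and grows with that share, from about 78–79% power at 5% to about 70–72% at 20% (exact to normal approximation).

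This rests on two-sided alpha of 0.05 applying to the benign outcome, on the article's own discordant rates, and on assumed shares. The analysis confined to definite benign outcomes will sit lower on that scale if many patients are only probable benign. It would go too far to call the 80% false as printed. The statement is true of 2026 benign patients, whom this study will not have.

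**What to change.** In the benign paragraph of the Sample size section:

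1. Say that 2026 refers to benign patients.
2. State the assumed percentages of the 2000 who will have cancer and who will remain indeterminate, with their basis.
3. Replace the statement of 80% power with 2026 individuals by the power at the resulting number of benign patients, given twice: with and without probable-benign patients.

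A possible form: *Of 2000 enrolled, we assume a% with cancer and b% indeterminate, leaving n benign patients (n′ if probable-benign patients are included); with discordant rates of 17.0% and 13.5% and a two-sided 5% level, power is P (P′).*

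This changes wording only. Design, enrolment and analysis stay as they are, and the cost is a slightly less favourable stated power.

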#### Statistical analysis

Statisticians will carry out all analyses. For each outcome measure, the following will be reported:

The number of participants included in the analysis, stratified by the relevant group.Mean or median (SD or IQR) for continuous outcomes, and numbers and proportions (percentage) for binary outcomes.An effect size (OR) with a 95% CI.A two-sided p value.

For both primary objectives, measured differences between standard care and the LCP options for patients with cancer diagnosed and benign-nodule patients discharged will be analysed using conditional logistic regression. Statistical significance will be assessed with a Wald test. Secondary outcomes will be described and analysed according to their distribution. All outcomes will have an exact p value provided for them so the reader can access the data for significance level, so correction for multiple testing should not be needed.

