Optellum has developed and extensively validated an AI-based computer-aided diagnostic (CADx) tool for lung cancer prediction (LCP) in pulmonary nodules, which has UK Conformity Assessed marking under UK medical device regulations. The AI model underpinning the LCP is a convolutional neural network (CNN), referred to hereafter as the ‘LCP-CNN’. LCP-CNN was derived and internally validated using data from diverse populations from the USA and UK. The model was then externally validated in two independent cohorts of patients with incidentally detected pulmonary nodules, amounting to over 1500 patients in aggregate.^7 8^ The LCP-CNN demonstrated greater accuracy in these studies than the Brock and Mayo malignancy risk models (used in managing incidentally detected nodules in the UK and USA, respectively). The product is provided within the ‘Virtual Nodule Clinic’ (VNC), a software device used in the tracking, assessment and characterisation of incidentally detected pulmonary nodules.

The study aims to assess this new AI tool in a prospective real-world setting in the UK. This will be done by calculating malignancy risk using LCP and measuring how management would differ if it was governed by the risk provided. The aim is to provide evidence as to whether LCP should be the new standard of care in pulmonary nodule management.

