In line with Standard Protocol Items: Recommendations for Interventional Trials - Artificial Intelligence (SPIRIT-AI) guidelines, performance errors that would have happened if the LCP or LCP-guided decision-making were part of standard care will be analysed and reported as outcome measures for the primary objective of this study.

Evaluation of LCP as threshold-based tests (scenarios #2 and #3 as described under AI model), which require access to LCP-CNN values, will be performed as a batch at the end of the study follow-up period. The threshold will be defined prospectively based on values from training datasets of similar patient populations. The use of the recommendation with physicians making the decision will be evaluated via a separate research meeting at the end of the 12-month follow-up period.

For cost-effectiveness modelling, quality of life data will be collected by inviting patients to complete an EQ-5D-5L quality of life questionnaire at two time points: (a) as close as possible to the baseline CT scan on which their pulmonary nodule was detected and (b) at a 1-year time point afterwards. A participant diary about primary care usage will also be collected at the 1-year mark.

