### Outcome measures

The outcome measures for the primary and secondary objectives are outlined in table 1.

**Table 1 T1:** Study objectives and outcome measures

Objective	Outcome measure
Primary: Determine the potential effect of the LCP on discharge	The measured difference between standard care and the three LCP-based options described under AI model for: No and percentage of cancer patients discharged (straight after assessment of the baseline scan). No and percentage of benign-nodule patients discharged (straight after assessment of the baseline scan).
Secondary: Determine the potential effect of the LCP on possible adherence to clinical guidelines	The measured difference between standard care and the three LCP-based options described under AI model: No and percentage of patients for whom a validated risk model (Brock or LCP) is used to guide the next clinical management step (ie, counting the instances where Brock is not used or where LCP is not possible to compute, or it is ignored).
Secondary: Determine the potential effect of the LCP on overall clinical management, as well as scan and procedure utilisation	No and percentage of cancer patients for whom there would have been a change in clinical management according to each of the three LCP-based options described under AI model compared with actual care (correctly for more aggressive management and incorrectly for less aggressive management). No and percentage of benign-nodule patients for whom there would have been a change in clinical management according to each of the three LCP-based options described under AI model compared with actual care (incorrectly by more aggressive management and correctly for less aggressive management). The measured difference between standard care and the three LCP-based options described under AI model for: No and percentage of CT scans and PET/CT scans performed on benign-nodule patients. No and percentage of non-surgical biopsies performed on benign-nodule patients. No and percentage of surgical excisions on benign-nodule patients.

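### For discharged cancers the plan fixes a matched odds ratio and a Wald test, which do not bound the excess in percentage points and often cannot be computed when cancers are few

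*Protocol article*

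**What the plan says.** Table 1 of the Protocol article lists, under the primary objective, the difference between standard care and each of three LCP options in "No and percentage of cancer patients discharged (straight after assessment of the baseline scan". The Data collection section makes "performance errors that would have happened if the LCP or LCP-guided decision-making were part of standard care" outcome measures of the primary objective. A cancer patient sent home is the most serious error of that kind. The Introduction gives the purpose: "The aim is to provide evidence as to whether LCP should be the new standard of care in pulmonary nodule management".

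For every outcome the Statistical analysis section asks for the number analysed, "numbers and proportions (percentage) for binary outcomes", and then "An effect size (OR) with a 95% CI.A two-sided p value". Both primary comparisons are to use conditional logistic regression, with significance judged by a Wald test. The Sample size section plans the cancer comparison as a McNemar difference test in which LCP discharges fewer cancers than the Brock threshold: "90% power and a significance level of 0.05, 659 participants would be needed".

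The article states no interval for the difference in percentages and no acceptable excess. It also does not say how a non-significant result would be interpreted.

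**The concern.** The measure that carries the confidence interval is not the quantity named in Table 1. With one pair of decisions per patient, the conditional odds ratio is the ratio of the two discordant counts, and the patients on whom both methods agree drop out. A reader deciding whether LCP could replace standard care needs to know how many more cancers per hundred might be discharged. The odds ratio interval does not say.

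The method is also fragile where this study is likely to be. The Abstract says only a small percentage of nodule patients have cancer, so discordant cancers will be few and one of the two cells may well be empty. The odds ratio is then zero or infinite and the Wald test is undefined. At stake is the one primary outcome that speaks to harm: it could end with no usable effect estimate, or with a non-significant p value that carries little information.

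**Working it through.** **Notation.** Among n cancer patients, b are discharged by the LCP option only and c by standard care only. Conditional logistic regression gives OR = b/c, SE(ln OR) = √(1/b + 1/c) and Wald z = ln(b/c) / √(1/b + 1/c).

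**Inputs.** Discordant rates of 0.4% and 2.6%, alpha 0.05, power 90% and n = 659 come from Sample size. Total recruitment of 2000 comes from Design and setting. The number of cancers is not given; I assume 100, 200 and 300 (5%, 10% and 15% of 2000), with 400 and 659 for comparison.

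**1. The plan's own figure.** The asymptotic McNemar formula gives
n = [1.960·√0.030 + 1.2816·√(0.030 − 0.022²)]² / 0.022² = (0.3395 + 0.2202)² / 0.000484 ≈ 648.
This is within 2% of the stated 659, at which power is 90.5%. The figure reproduces, and it is a number of cancer patients.

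**2. What the odds ratio interval leaves out.** Take b = c = 2. Then OR = 1.0 and SE = √(1/2 + 1/2) = 1, so the 95% CI is e^(±1.96) = 0.14 to 7.1 for any n. For the paired difference d, the Tango score limits solve (b − c − nd) / √(n[2q + d(1 − d)]) = ±1.96, where q is the constrained estimate of the standard-care-only rate. The upper limits are +5.3, +2.7 and +1.8 points with 100, 200 and 300 cancers. One odds ratio interval covers three quite different degrees of reassurance.

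**3. How often there is no finite odds ratio.** Reverse the plan's difference, so that LCP only is 2.6% and standard care only is 0.4%. The chance that at least one discordant cell is empty is
0.974ⁿ + 0.996ⁿ − 0.970ⁿ.
- n = 100: 0.072 + 0.670 − 0.048 = 0.694
- n = 200: 0.005 + 0.449 − 0.002 = 0.451
- n = 300: 0.0004 + 0.3005 − 0.0001 = 0.301

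An empty cell can matter. With 6 against 0, the exact McNemar p value is 2 × 0.5⁶ = 0.031, while the Wald test has no value.

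**4. How often the excess is missed.** I enumerated the binomial distribution of b and c and counted a result as detection if it was significant at two-sided 0.05 in the harm direction. Empty cells count as no Wald result.

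| Cancers | No finite OR | Wald misses | Exact McNemar misses | Uncorrected (score) McNemar misses |
|---|---|---|---|---|
| 100 | 69% | 99.9% | 97% | 82% |
| 200 | 45% | 94% | 75% | 55% |
| 300 | 30% | 74% | 51% | 37% |
| 400 | 20% | 50% | 33% | 24% |
| 659 | 7% | 14% | 9% | 6% |

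**5. A larger excess.** At 4.5% against 1.0% (3.5 points), the Wald test misses 32% with 300 cancers and 15% with 400. The exact test misses 86%, 54% and 31% with 100, 200 and 300.

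**6. An example.** With 200 cancers and 5 against 1 discordant, OR = 5.0, SE = √(1/5 + 1) = 1.095, 95% CI 0.58 to 42.8, z = 1.609/1.095 = 1.47, p = 0.14. The paired difference is (5 − 1)/200 = +2.0 points, with Tango limits of −0.6 and +5.3. The second statement tells the reader what excess remains possible.

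**The case against.** The article is condensed and a statistical analysis plan may exist, so a paired-difference interval could appear there. That would answer a complaint about missing detail. Here, however, the article names the effect measure and the test, and those are what perform badly.

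A difference test fits the stated hypothesis. The sample size expects LCP to discharge fewer cancers, and Table 1 speaks of a difference. This stands: a non-inferiority margin is a debatable choice in a non-interventional study framed this way, and its absence is not an error.

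Counts and percentages are also reported, so an excess would be visible, and a reader with the number analysed, the counts by method and the odds ratio could often rebuild the interval. That is true, but the route runs through an odds ratio that frequently will not exist, and the plan should not leave the key interval to the reader.

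The low power comes mainly from few cancers. This also stands. With 659 cancers, McNemar's test has about 90% power in either direction, and a score interval does not cure scarcity: the score test in the table still misses the 2.2-point excess in 82%, 55% and 37% of studies with 100, 200 and 300 cancers.

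A reader might infer that the plan treats a non-significant result as proof of safety, or that such a result is likely however many cancers LCP misses. The documents support neither. No such reading of the p value is stated, and with about 300 or more cancers and a 3.5-point excess, harm would more likely than not be detected.

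**Conclusion.** The point holds in a limited form. For cancer patients discharged, the only interval the plan fixes is on a matched odds ratio. That interval does not bound the excess in percentage points, although Table 1 names the difference in percentage. With an assumed 100, 200 or 300 cancers and a 2.2-point excess, the odds ratio and its Wald test would be unavailable in about 69%, 45% and 30% of studies, and the planned test would miss the excess in about 99.9%, 94% and 74%. A non-significant result at those counts would say little about safety.

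These sizes rest on the assumed cancer counts and on the plan's discordant rates taken in reverse. They shrink as cancers or the true excess increase. The choice of the Wald test adds to a problem whose main source is the small number of cancers.

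**What to change.** For cancer patients discharged, and for each LCP option:

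- Make the paired difference in percentages (LCP option minus standard care), with a score (Tango-type) 95% CI, the main effect measure.
- Replace the Wald test with an exact or score McNemar p value.
- Keep the matched odds ratio as a supporting figure where it is finite.
- State that any conclusion about excess discharged cancers rests on the upper confidence limit, and that a non-significant p value is not evidence of safety.

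A pre-stated acceptable excess, set by the clinical leads, is optional. It would give the upper limit something to be judged against.

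The cost is a paragraph in the analysis plan and a few lines of code, with no new data. The downside is that with few cancers the upper limit may be too wide to support any safety statement. The study would then have to report that openly.
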